#### EuroQuol – 5 Dimensions – 5 Levels

The EQ-5D-5 L [36] is the most recently developed version of the EQ-5 Dimensions [48, 49], which is a standardised measure of health status that has good construct validity and responsiveness among people with chronic pain [50]. Developed by the EuroQol group, it is supported by the National Institute for Clinical Excellence (NICE) for measuring change in health-related quality of life with various patient groups [51], has been validated within numerous patient groups including the chronic pain population, and has been shown to be a sensitive tool with internal consistency and reliability [52–55].

#### The Brief Pain Inventory

The BPI [34] is an easy to use tool for the assessment of pain in both clinical and research settings and uses simple numeric rating scales from 0 to 10 (with 0 = no pain to 10 = pain as bad as you can imagine). The BPI has been used internationally [34, 56, 57] to measure severity and interference of pain in patients who live with a range of chronic pain presentations.

#### Pain Catastrophizing Scale

The PCS [35] is a 13-item scale consisting of statements regarding the thoughts and feelings that patients report when they experience pain scored from 0 (not at all) to 4 (all the time). Total PCS scores range from 0 to 52 points and higher scores indicating higher levels of pain catastrophizing. The PCS consists of three subscales, which are magnification, rumination, and helplessness. The scale was developed to be used within both clinical and non-clinical populations and was originally an elaboration on the Coping strategies Questionnaire [58]. The PSC has been shown to have reliability and validity in both pain populations and healthy adult populations with a high internal consistency [59].

#### Brief measures to be completed before and after audio in clinic and the last session during the first week at home

Three brief, single-item measures are used to assess level of distractedness, pain severity and pain distress. Patients are asked to rate “How distracted do you feel right now?” (devised specifically for this study), “How severe are your pain related symptoms right now?”, and “How distressing are your pain related symptoms right now?”, all on a scale from 1 (not at all) to 7 (extremely so).

### Statistical analysis

We will present the baseline characteristics according to the two study groups. For the analysis assessing the immediate effects of the intervention, we will assess the effect of the body scan versus the control intervention on ratings for the brief psychological measures administered immediately before and after the interventions. This analysis will be conducted for the ‘before’ and ‘after’ ratings in the clinic and also for those conducted in the participant’s own environment. First, we will compute change scores by subtracting post-intervention scores from pre-intervention scores. As it is a pilot study with a small sample size, initially we will assess the effect of the treatment groups on outcomes (i.e. change scores) using *t* tests or Mann–Whitney tests. We will then conduct multiple linear regressions with the change scores as the dependent variables and treatment groups as the independent variable. Statistical significance will be assessed with the likelihood-ratio test, with the estimate of effect given as mean difference of change scores and 95 % confidence interval. As a secondary analysis we will adjust for age, sex and baseline BPI score, as potentially important prognostic baseline factors. We will also inspect the baseline characteristics, for the two groups, to assess whether there are any other potential confounders that need to be controlled for.

Next, we will assess the effect of the study groups on outcomes recorded at baseline and one month. All participants with data at both time points will be included in the analysis. It is unlikely that the study will be sufficiently powered to detect significant differences between the groups but we will carry out analyses in order to inform parameters for a definitive trial. We will compute change scores between baseline and one month for the HADS, EQ-5D-5 L, PCS and the CAMS-R, and we will conduct multiple regressions, with adjustments as above. We will also repeat this procedure for the CAMS-R at baseline and one week.

Before conducting any of the regression analyses, we will assess the distribution of residuals of the dependent variable(s). We will use the bootstrap method if the distribution of the residuals of the dependent variable in any regression model is not normal. In the case of missing data at one week or one month, we will conduct a sensitivity analysis, in which we will use multiple imputation to impute values for those with missing data for any variables.

We will use *t* tests or Mann–Whitney tests to compare scores for ratings of ‘usefulness’ and for whether participants would recommend the intervention. All data will be analysed using SPSS V19, with the level of significance set at *P* < 0.05.

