### Sample size

It is recommended that pilot/feasibility studies ideally recruit a total of at least 50 participants [20], although in practice many studies recruit 50–100 participants. We aim to recruit 90 participants (45 in each treatment arm). Then, allowing for 10 participants withdrawing (estimate based on a previous mindfulness study with the same population [27]), we aim to have around 80 participants with data through to the final one month follow-up. Moreover, based on a finding from a previous similar study [27], we used a Wilcoxon signed-rank test (G-Power software) to calculate that a total sample size of at least 50 participants would be required to detect a significant difference of 1.2 (SD = 2) on the perceived distress scale, between the two groups (immediately) after the intervention. This was with 80 % power at the 5 % significance level.

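### Change scores are compared without adjusting for the outcome's own baseline, which gives up precision, and further covariates are left to an open choice after inspecting group differences

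*Protocol article*

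**What the plan says.** All of this is in the Statistical analysis section of the protocol article.

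- **Outcome form:** "First, we will compute change scores by subtracting post-intervention scores from pre-intervention scores". This covers the three brief ratings, in clinic and at home. Change scores are also used for HADS, EQ-5D-5L, PCS and CAMS-R at one month, and for CAMS-R at one week.
- **First model:** after t or Mann–Whitney tests, "We will then conduct multiple linear regressions with the change scores as the dependent variables and treatment groups as the independent variable".
- **Adjusted model:** "As a secondary analysis we will adjust for age, sex and baseline BPI score, as potentially important prognostic baseline factors".
- **Further covariates:** baseline characteristics are compared between the groups "to assess whether there are any other potential confounders that need to be controlled for". No candidate list, criterion or limit is given.
- **One-month outcomes:** "we will conduct multiple regressions, with adjustments as above". The stated purpose is that "we will carry out analyses in order to inform parameters for a definitive trial".

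The Sample size section bases power on a between-group comparison, "to detect a significant difference of 1.2 (SD = 2) on the perceived distress scale", with 45 per arm recruited and about 80 patients expected at one month. It does not say whether the SD is that of the raw rating or of its change.

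**The concern.** There are two separate issues.

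**Missing covariate.** The baseline value of the outcome is usually its strongest predictor, and here it is already measured. A regression of change on group alone gives the same mean difference as the t test before it, so it adds no precision. A change score fixes the slope on baseline at 1. When the true slope is below 1, an arm that starts higher by chance appears to improve more, simply through regression to the mean. BPI, age and sex stand in only partly for the own baseline.

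**Open covariate choice.** Under randomisation, baseline differences arise by chance. Covariates are better chosen in advance for their prognostic value than afterwards for their imbalance. With no rule, several models are available and the reported estimate can depend on which one is picked.

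Both issues matter despite the pilot label. The immediate effects are one of two primary objectives and carry a significance hypothesis, and the one-month estimates are meant to feed the design of a definitive trial.

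**Working it through.** **Inputs.** Difference 1.2 and SD 2, so d = 1.2/2 = 0.6; 45 per arm (Sample size section). Two-sided 5% is assumed, since sidedness is not stated. The before–after correlation r is not in the article, so a range is assumed. Before and after variances are taken as equal (s²).

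**The plan's own figure.** The stated minimum of 50 in total does not reproduce as a two-group requirement. At d = 0.6 a two-sample t test needs 45 per arm (90 in total). The figure 50 arises as 2 × 25, where 25 is the paired signed-rank requirement within one group. That is a separate matter and nothing below depends on it.

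**Variance.**
- Change score: 2s²(1−r)
- ANCOVA on own baseline: s²(1−r²)
- Ratio: (1−r²)/[2(1−r)] = (1+r)/2

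The ratio is 0.75 at r = 0.5, 0.85 at 0.7, 0.90 at 0.8 and 0.95 at 0.9. Confidence intervals shrink by its square root, to 87%, 92%, 95% and 97% of the change-score width.

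**Power at 45 per arm** (noncentral t).
- Reading A, SD 2 is the SD of change: effect size 0.6 for change and 0.6/√((1+r)/2) for ANCOVA.
- Reading B, SD 2 is the SD of the raw rating: 1.2/[2√(2(1−r))] for change and 1.2/[2√(1−r²)] for ANCOVA.

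| r | A: change | A: ANCOVA | B: change | B: ANCOVA |
|---|---|---|---|---|
| 0.5 | 80% | 90% | 80% | 90% |
| 0.6 | 80% | 88% | 88% | 94% |
| 0.7 | 80% | 86% | 95% | 98% |
| 0.8 | 80% | 84% | 99% | 100% |

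Under reading A with 40 per arm, power rises from 75.5% to 86.4% at r = 0.5 and to 79.8% at r = 0.8.

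**Chance imbalance.** If the arms differ by δ at baseline, the after scores are expected to differ by rδ, so the change-score estimate shifts by (1−r)δ. One standard error of imbalance at 45 per arm is √(2/45) = 0.21 SD. The shift is 0.5 × 0.21 = 0.11 SD at r = 0.5 and 0.2 × 0.21 = 0.04 SD at r = 0.8.

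**BPI as a substitute.** Suppose BPI relates to the outcome only through the outcome's baseline, with correlation b to that baseline. In units of s², the residual variance of change given BPI is 2(1−r) − [b(1−r)]². At r = 0.5 this is 0.98, 0.94 and 0.88 for b = 0.3, 0.5 and 0.7. The unadjusted change score has 1.00 and the own-baseline ANCOVA 0.75.

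**Covariate choice.** An illustrative simulation under no treatment effect used 80 patients, 6,000 runs, three fixed covariates, six candidates and assumed covariate effects. Rejection rates at the 5% level were:
- unadjusted 5.6%; prespecified covariates 5.3%
- adding any candidate imbalanced at p < 0.1: 4.6%
- most favourable of those three models: 7.7%
- most favourable of the unadjusted, prespecified and six single-addition models: 9.8%

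**The case against.** Most of the case on the other side is right, and it limits the point.

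- **Bias.** A reader might infer that the change-score result is biased. It is not: under randomisation the group difference in change is unbiased on average. The imbalance shift describes a single unlucky allocation.
- **Power.** A reader might infer that the trial is at or below 80% power as planned. That needs the SD of 2 to be the SD of change, which the article does not say. It describes a between-group difference just after the intervention, which can equally be read as the SD of the raw rating. On that reading change scores exceed 80% power once r is above about 0.5, and the gain from ANCOVA at r of 0.7 or more is a few points or less.
- **Type I error.** A reader might infer that inspecting imbalance inflates the false-positive rate. In the simulation a fixed imbalance rule did not. Inflation came only from reporting the most favourable model, which the protocol nowhere proposes. For the immediate effects the adjusted model is labelled secondary, and a statistician blinded to allocation does the initial analysis of the main outcomes.
- **Home session.** ANCOVA on the home pre-audio rating would be a mistake. That rating precedes the last session of the first week, so it follows randomisation and earlier audio use, and treatment may have changed it.
- **Pilot status.** The article itself says the one-month comparisons are unlikely to be adequately powered.

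What remains is that the model is stated outright, its covariate list leaves out the most useful variable, and the one-month regressions carry the same list. The inspection step could bring in an own baseline, but only where the groups happen to differ on it. That is the wrong reason to include it.

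**Conclusion.** The point holds as one of efficiency and prespecification. Every outcome with a before value is analysed as change, and the outcome's own baseline is in no specified model. The cost is precision and some exposure to chance imbalance. Residual variance could be about 25% lower at r = 0.5, 15% at 0.7 and 5% at 0.9, assuming equal before and after variances and an r the article does not give.

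At 45 per arm, power rises from about 80% to 90% (r = 0.5) or 84% (r = 0.8) if the SD of 2 is that of change. If it is the raw SD, the gain is the same at r = 0.5 and only a few points at 0.7 or above. The (1+r)/2 figures apply to the clinic, one-week and one-month outcomes. They do not carry over to the home session, where the valid covariate is an earlier rating.

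The covariate-selection concern is the open choice among models. Blinding and, for the immediate effects, the secondary label soften it. It weighs more at one month, where the adjusted regression is the analysis described.

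**What to change.** - **Clinic, one-week and one-month outcomes:** make the main model an ANCOVA of the follow-up score (or, equivalently for the treatment effect, the change) on treatment group and the baseline score of the same outcome, with age, sex and baseline BPI as the fixed further covariates. Report the adjusted mean difference with its 95% CI, using the bootstrap for non-normal residuals as already planned.
- **Home session:** adjust for the clinic pre-audio rating, not the home pre-audio rating. State whether the dependent variable is the home post-audio rating or the within-session change, because with this covariate the two answer different questions.
- **Sensitivity analyses:** keep the t or Mann–Whitney tests and the unadjusted change-score differences here.
- **Covariate search:** delete the step that compares the groups to find more covariates, or label it a sensitivity analysis.

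The cost is a change of wording in the analysis section. The baseline scores are already collected, and neither the sample size nor the visit schedule changes.

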### Procedure in clinic

Patients who meet the inclusion criteria are approached by the research team and given a patient information sheet regarding the study. Patients are given as much time as they want to consider whether they want to participate and written consent is obtained from all patients who agree to do so. Delivery of the intervention is standardized, with a researcher checklist (i.e. written manual) including a step-by-step script developed to address fidelity issues. This script and checklist are used during recruitment and researchers observed each other administering the intervention to at least one patient each so as to standardize procedures.

As detailed previously, an initial face-to-face visit is conducted in a private room or cubicle at St George’s Hospital or St John’s Therapy Centre. Patients are randomized to either the control or treatment group and asked to complete baseline measures, including brief psychological measures, and to listen to the relevant audio once in clinic with the researcher. After listening to the audio, patients are asked to complete the brief psychological measures again. Before leaving, patients are advised to consider barriers and solutions to use of the audio in their own environment and are given a study packet to take home. They are instructed to use the audios as a self-management tool and to try the audio during particularly painful times if possible. The contents of the study packet containing follow-up questionnaires (i.e. Study Diaries 1–3), self-addressed prepaid return envelopes and brief instructions, are then reviewed with the patient in case there are any queries. If the audios are not directly downloaded to a personal device, patients are allowed to keep the MP3 players if they want after they finish, as they are a minimal cost. The offer of the MP3 player is not mentioned in the patient information sheet, and therefore is not considered as an incentive to recruitment.

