#### Measures to be completed during and after one month

Study Diary 3 includes another self-monitoring table where patients can continue to detail date, time and position of use of the audios during the three weeks prior to the final 1 month follow-up. At 1 month, items regarding pain self-efficacy and physical function are repeated in addition to the measures of mood, pain catastrophizing, mindfulness, and HRQoL that were administered at baseline. While one week is likely too brief for patients to make (meaningful) changes in physical and/or psychological function, assessment after the completion of the intervention (one month) will better allow for the detection of changes in function where they have occurred.

A brief assessment of whether they have continued listening to the audio (and if so, how often), a discussion of the main barriers to and facilitators of use, and their view on the beneficiality of an online support group forum, texting support and more face time, is conducted with a brief (around 5 minutes) open-ended telephone interview. A schedule of assessment for all measures included is presented in Table 1 below.

**Table 1 Tab1:** Schedule of data and measurement collection

Measure	Baseline	During week	At 1 week	During month	At 1 month
Background and pain-related questionnaire	X				
Pain self-efficacy item	X				X
Pain and physical function item	X				X
Mood questionnaire (HADS)	X				
Mindfulness questionnaire (CAMS-R)	X		X		X
Pain-specific questionnaire (BPI)	X				
Pain catastrophizing questionnaire (PCS)	X				X
Health-related quality of life questionnaire (EQ-5D-5L)	X				X
Brief psychological measures (two times, before and after intervention)	X	X			
Experience of audio items			X		
Previous experience			X		
Self-monitoring table		X		X	

HADS, Hospital Anxiety and Depression Scale; CAMS-R, Cognitive and Affective Mindfulness Scale Revised; BPI, Brief Pain Inventory; PCS, Pain Catastrophizing Scale; EQ-5D-5 L, EuroQuol – 5 Dimensions – 5 Levels

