### Debrief at one month

Patients are followed up after one month by telephone for a study debrief. Patients are debriefed regarding the full nature of the study and, if they are part of the control group, they are offered to have the intervention audios sent to them in case they wish to try them. Resources that are readily available to the public are recommended at this time if patients wish to further explore mindfulness. Patients are reminded to complete and post back the questionnaires.

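### The main one-month analysis keeps only patients who post back their forms; if return depends on use or early benefit and differs by arm, the effect sizes for the definitive trial may be biased

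*Protocol article*

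**What the plan says.** The Statistical analysis section of the Protocol article plans change scores from baseline to one month for HADS, EQ-5D-5L, PCS and CAMS-R. It fixes the set for this analysis: "All participants with data at both time points will be included in the analysis". It accepts that power at one month will probably be low and gives the purpose: "we will carry out analyses in order to inform parameters for a definitive trial". For data missing at one week or one month, it adds: "we will conduct a sensitivity analysis, in which we will use multiple imputation to impute values for those with missing data for any variables".

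The route by which the scores arrive is set out in other sections:

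- Procedure in clinic: the packet taken home holds "follow-up questionnaires (i.e. Study Diaries 1–3), self-addressed prepaid return envelopes".
- Measures to be completed during and after one month, on what the third diary holds: "Study Diary 3 includes another self-monitoring table where patients can continue to detail date, time and position of use of the audios". The same paragraph continues: "At 1 month, items regarding pain self-efficacy and physical function are repeated in addition to the measures of mood, pain catastrophizing, mindfulness, and HRQoL".
- The one-month telephone interview asks whether and how often the patient still listens. No outcome scale is described as part of it.
- Debrief at one month: "Patients are reminded to complete and post back the questionnaires".

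CAMS-R is also measured at one week, in Study Diary 2. The main one-month change score makes no use of it.

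**The concern.** The one-month scales appear to share a posted diary with the log of audio use. A patient who has stopped listening has an empty log and may feel there is nothing to send back. If so, the patients with both time points are weighted towards continuing users, and the main estimate describes them more than the groups as randomised.

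The article names estimation of effect sizes as part of the feasibility assessment. If the one-month effect is overstated and the definitive trial is sized on it, that trial will have less power than planned. The complete-case rule also discards a patient who has baseline and week-1 CAMS-R but no month-1 form, although the week-1 score carries information on early response.

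**Working it through.** **Plan's own figure.** Sample size section: 90 recruited, 45 per arm, 10 withdrawals allowed. 90 − 10 = 80, which agrees with the stated figure of around 80 at one month. Loss is 10/90 = 11.1%. The split by arm is not given.

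**Simple model (assumed).** Continuing listeners in the mindfulness arm have effect D, stoppers have none, and controls are unaffected. L is the share who keep listening; r_L and r_N are the return rates of listeners and stoppers.

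Complete-case effect ÷ full-cohort effect = r_L / [L·r_L + (1 − L)·r_N]

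The largest value, reached when every lost patient is a stopper, is 1/(1 − loss).

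- 5 of 45 lost in the mindfulness arm: 45/40 = 1.125.
- All 10 lost in that arm: 45/35 = 1.286.
- L = 0.6, r_L = 0.95, r_N = 0.80 (89% return overall): 0.95/0.89 = 1.067.
- Same return rates, but stoppers keep half the benefit: 1.025. They keep all of it: 1.00. They do better, at 1.5 times D: 0.983.
- Return unrelated to listening: 1.00.
- Stoppers return more often (95% against 85%): 0.93 to 0.98 for L between 0.4 and 0.8.

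**Effect on a definitive trial.** Take a trial planned at 80% power, two-sided 5%, on an effect overstated by factor f. Its true power is Φ(2.8016/f − 1.96), where 2.8016 = 1.96 + 0.8416.

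- f = 1.125: Φ(0.530) = 70.2%.
- f = 1.286: Φ(0.219) = 58.7%.

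**Does the week-1 CAMS-R help?** This was simulated with assumed inputs: 45 per arm, true effect 0.40 SD at one month and 0.30 SD at week 1, correlations 0.5 to 0.7. The comparison is the complete-case change score against predicting missing month-1 values from baseline and week 1, by arm. Ranges reflect the strength of selection.

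| Loss | Complete case (SD) | Using week 1 (SD) |
|---|---|---|
| Unrelated to outcome | 0.40 | 0.40 |
| 11%, mindfulness-arm loss follows week-1 gain | 0.46–0.51 | 0.39–0.41 |
| 25% in mindfulness arm, follows week-1 gain | 0.48–0.64 | 0.39–0.41 |
| 25% in mindfulness arm, follows change after week 1 | 0.49–0.57 | 0.52–0.62 |

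With the same selection rule and the same loss in both arms (11% or 25%), the complete-case estimate is 0.39–0.41 SD, so there is no bias. The standard error is about 0.23 SD for either method, and using week 1 did not raise it.

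Two cautions on reading these figures. The 12.5% is a ceiling for the simple model only. When loss follows individual gain, which includes chance variation, the complete-case figure at 11% loss can exceed it: 0.46/0.40 = 1.15 to 0.51/0.40 = 1.28. And 25% of 45 is about 11 patients, more than the 10 losses planned for the whole trial.

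**The case against.** A reader might infer three stronger things that the article does not support.

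- **That only returners are ever analysed.** This is wrong. Multiple imputation is planned, though as a sensitivity analysis. Which variables enter the imputation model is ordinary SAP content, so their absence from a protocol article is not a fault.
- **That stoppers do drop out selectively and the effects are inflated.** No section gives return rates by listening, by arm or by outcome. Controls get the same request to listen and may stop too, and equal selection with equal loss cancels. The direction could even reverse.
- **That follow-up neglects patients who stop.** The packet is reviewed with each patient in clinic, the one-week call encourages diary keeping, and the reminder at one month is not limited to listeners. Forms can arrive after it. That the scales are bound into Study Diary 3 is a fair reading of two sections, but it is not stated outright.

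The size is also modest. An extra 12.5% on 0.40 SD is 0.05 SD, about a fifth of the standard error. Week-1 CAMS-R is itself in a posted diary, so some non-returners will lack it. If patients are lost because of what happens after week 1, the week-1 score does not rescue the estimate. Scores taken by telephone would pass through an unblinded researcher, whereas the Discussion relies on self-report to limit that bias.

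All of this stands against the stronger readings. It does not change the fact that the plan makes the complete-case result the main one while holding an intermediate score that could be used at no loss of precision.

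**Conclusion.** The point holds as a modest improvement, not as a demonstrated error. The main one-month analysis is complete-case on posted forms, imputation is secondary, and the estimates feed a definitive trial. If return depends on continued use or early benefit and differs between arms, the effect sizes may be biased, probably upward.

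At the planned loss split evenly, the overstatement is at most 12.5%, on the assumptions that every lost mindfulness patient had no benefit and that controls are unaffected. A later trial planned at 80% would then have about 70% power. The 1.286 and 59% case needs all 10 losses in one arm, which nothing in the article suggests. Using the week-1 CAMS-R removes the bias when loss follows week-1 gain, costs no precision when there is no bias, and does not help when loss follows later change.

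**What to change.** 1. **CAMS-R.** Make the main one-month analysis a mixed model over baseline, week 1 and month 1, including all randomised patients with any post-baseline score. Keep the complete-case change score as secondary.
2. **Other scales.** In the imputation already planned, include the week-1 CAMS-R and reported use (from the week-1 diary and the one-month call), by arm. This can be written in the SAP.
3. **Follow-up.** At the one-week call, tell every patient that the one-month questionnaires are due even if they have stopped listening. Separating the outcome forms from the use log is a minor further option.
4. **Optional.** In the existing one-month call, before the debrief, collect CAMS-R and EQ-5D-5L from patients unlikely to return the form, and record the collection mode.

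The cost is a little more analysis work and a sentence or two in a call already being made. Item 4 carries possible mode and unblinded-researcher effects, which is why it is optional. No item protects against loss that depends on changes after week 1, and the report should say so.
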